### Participants and recruitment process

2.4

Participants for this RCT study are recruited from public and private organizations within a management consultancy network in Denmark, including national and international leaders. The recruitment process involves contacting HR Management via email or phone and introducing the program to interested organizations. Interested HR managers receive materials to engage internal unit managers, who is invited to participate if they express interest. To ensure unbiased selection, all leaders from enrolled units are invited to voluntarily sign up for the local resilience training program.

Inclusion criteria:

Age 18 or aboveFormal leadership role or indirect leadership responsibilityWillingness to participate in an RCT study and complete anonymous questionnairesCommitment to the resilience programAttendance of weekly 1-h sessions during the intervention periodEngagement in resilience training within a peer community

Exclusion criteria:

Late sign-up after the recruitment periodBeing on sick leave during recruitment and introductionLack of commitment to the scheduled training interventionWithdrawal of consent to participate

### Randomization of participants

2.5

Following guidelines from a previous meta-review on resilience training in organizational contexts (Robertson et al., 2015), individual participants from organizational units will be randomly assigned to either the experimental or control group using computer-generated simple randomization. To mitigate contamination risks, the intervention group will from the beginning be advised not to share intervention content and training materials with the control group. HR-business partners will monitor the participating units, where leaders also work across the organization in many diverse team compositions, which we expect can reduce direct interaction, intervention conversations, and spill-over effects. Both groups will continue with their regular job responsibilities; however, the experimental group will also participate in weekly training sessions and additional self-directed training between sessions. The control group will only complete questionnaire measurements before, during, and after the intervention. After the final measurement, control group participants will be offered a condensed period of resilience training. This behavioral intervention study will be reported using an extension of the CONSORT Statement for social and psychological interventions (Montgomery et al., 2018).

### Materials

2.6

#### Qualifying the measurements tools

2.6.1

To ensure contextual relevance, all outcome measurements, curricula, materials, and activities will be aligned with corporate language requirements, utilizing original and translated validated questionnaires for both Danish and English-speaking organizations. One necessary questionnaire will be translated into Danish following the forward-and back-translation guidelines (Beaton et al., 2007). Further, we will employ the Rasch methodology (Rasch, 1960) to assess the psychometric properties of the questionnaires. Recognized in Business and Management Studies for handling subjective, ordinal, and non-observable variables (García-Pérez and Yanes-Estévez, 2022), the Rasch model allows for constructing a unidimensional scale based on participants’ evaluations and testing the fit of the sample data to this model (Stemler and Naples, 2021). Using the software package RUMM2030 (Andrich et al., 2009), we will specifically use the Polytomous Rasch model that examines the likelihood of individual leaders providing endorsement responses to each test item, considering unequal difficulty levels of endorsement across test items (Boone et al., 2014).

#### Primary outcomes

2.6.2

In this study, we adopt a comprehensive approach to assess the capacity and demonstration of resilience by employing two distinct measurement strategies. We directly measure resilience outcomes using specific resilience scales and, further we assess resilience-related outcomes, signaled by wellbeing and performance indicators (Vanhove et al., 2016). In total, this assessment design aligns with our foundational resilience model focusing on outcomes relevant to resilience in organizational settings (Britt et al., 2016; Kuntz et al., 2016).

##### Perceived stress

2.6.2.1

To assess participants´ perceived stress levels and their coping abilities, resources, and sense of control in the period, we will use the 10-item Perceived Stress Scale (PSS-10) (Cohen et al., 1983). This scale includes both negatively phrased items (e.g., “In the last month, how often have you felt nervous and stressed?”) and positively phrased items (e.g., “In the last month, how often have you felt that you were on top of things?”). Participants will rate their agreement with each statement on a 5-point Likert scale, ranging from 0 (never) to 4 (very often). The total score, ranging from 0 to 40, will be calculated by reversing the ratings for the positively phrased items. Higher scores indicate a higher level of perceived stress. The Danish version of the scale has been previously validated (Olsen et al., 2004) and used in research by the National Institute of Public Health in Denmark (Nielsen and Randall, 2013).

##### Psychological resilience

2.6.2.2

We will use the CD-RISC 10 scale, a shortened version of the original 25-item CD-RISC (Connor and Davidson, 2003; Campbell-Sills and Stein, 2007), to assess resilience as a personality trait for effectively coping and thriving in the face of adversity. The Danish version of the scale was obtained from a previous translation (Lauridsen et al., 2017) for research purposes. This scale measures several aspects of resilience, including flexibility, self-efficacy, emotional regulation, optimism, and cognitive focus under stress. Participants rate each item on a 5-point Likert scale, from 0 (not true at all) to 4 (true nearly all the time), with total scores ranging from 0 to 40. A higher total score indicates a higher level of resilience in individuals.

##### Resilience at work

2.6.2.3

To measure resilience at work, we will use the RAW scale (Winwood et al., 2013), which assesses resilience in the context of emotional distress. Resilience is viewed as a dynamic resource that can be developed at work through targeted skill training, emphasizing that resilience behaviors and strategies are not solely determined by genetic and personality factors. The RAW scale includes 20 items covering seven aspects: energy, self-care, adaptability, purpose, network, authenticity, and support. Participants rate each item on a 7-point Likert scale, from 1 (strongly disagree) to 7 (strongly agree), with higher scores indicating higher resilience capacity at work. The RAW scale will be translated into Danish with permission from the authors and following recommended guidelines (Beaton et al., 2007; Sousa and Rojjanasrirat, 2011). Further, it will be validated through Rasch analyses to ensure its psychometric properties and appropriateness for the resilience study.

##### Mental well-being

2.6.2.4

We will assess mental well-being using the Warwick-Edinburgh Mental Well-Being Scale (WEMWBS) (Tennant et al., 2007). This scale includes 14 positively worded items covering hedonic (feeling) and eudemonic (functioning) aspects such as positive affect, satisfying interpersonal relationships, and positive functioning. Participants rate each item on a 5-point Likert scale, from 1 (none of the time) to 5 (all the time), with total scores ranging from 14 to 70. Higher scores indicate higher mental well-being. The Danish version has been used in the European Social Survey (ESS) and validated by the National Institute of Public health in Denmark (Nielsen and Randall, 2013).

##### Flourishing

2.6.2.5

To measure positive mental health and well-being, we will use the 10-item Flourishing scale (Huppert and So, 2013), which assesses hedonic and eudemonic dimensions including competence, emotional stability, engagement, meaning, optimism, positive emotions, positive relationships, resilience, self-esteem, and vitality. Most items are rated on a 5-point Likert scale, from 1 (strongly disagree) to 5 (strongly agree). Exceptions are positive emotional stability and vitality rated on a 4-point Likert scale, from 1 (none or almost none of the time) to 4 (all or almost all of the time) and positive emotions, rated from 0 (extremely unhappy) to 10 (extremely happy). Higher scores indicate higher levels of flourishing. The Danish version has been used in the European Social Survey (ESS) and validated by the National Institute of Public health in Denmark (Nielsen and Randall, 2013).

#### Secondary outcomes measurements

2.6.3

During the training period, the intervention group will engage in continuous evaluation of the resilience training. The aim is to better understand the processes and mechanisms of change when training resilience in extreme times with leaders.

##### Evaluation of implemented resilience factors and training effectiveness

2.6.3.1

The program incorporates subcategories derived from the three main resilience components, allowing us to explore their relevance as training mechanisms. For this, we use the Kirkpatrick scale (Kirkpatrick and Kirkpatrick, 2016), a widely recognized evaluation model applicable in various training contexts (Alsalamah and Callinan, 2022) and for leadership development (Lacerenza et al., 2017). This scale includes four levels: reaction, learning, behavior, and results indicating effective training (Level 1–2) and training effectiveness (Level 3–4) (Kirkpatrick and Kirkpatrick, 2022). We operationalize this flexible model into a simple four-item measurement supplemented by an open-ended item for comments or qualitative responses. At the start of each training session, participants will reflect upon their adverse experiences and coping behaviors since the last session. They will then share and discuss resilience strategies with peers and trainers to learn from it. Finally, they will evaluate their weekly training, forming a cyclic learning and development process termed the “leader resilience-sprint.” The objectives of this evaluation part, include identifying the most relevant resilience-promoting factors from a training content perspective, understanding the training and learning mechanisms during intervention, and providing self-monitored progress feedback to potential enhance motivation, goal pursuit, and reduce dropout rates (Locke and Latham, 2019; de Jong et al., 2021).

##### Process evaluation of influencing factors on leader resilience processes

2.6.3.2

Aligned with previous recommendations (Robertson et al., 2015), we explore factors influencing change during resilience training viewing resilience as dynamic and shaped by contextual and person-environment interactions (Förster and Duchek, 2017; Robertson et al., 2015). To identify the individual and organizational mechanisms that may hinder or facilitate intervention change (Nielsen and Randall, 2013), we will conduct a process evaluation that adapts to the specific intervention context (Arends et al., 2014). Data is collected from questionnaires at two timepoints (T1 and T2), as process elements may evolve over time (Nielsen and Randall, 2013). The questionnaires, discussed within the research team, are outlined by micro-processes (intervention implementation), macro-processes (design, delivery, maintenance), and intervention context (organizational and external conditions) following a guiding framework for analyzing process data (Randall et al., 2007). Process evaluations can complement effect evaluations in a mixed method design (Nielsen et al., 2010), helping to explore factors impacting the intervention outcomes (Nielsen and Randall, 2013). Furthermore, at T2, we will assess the intervention’s usability through open-ended questions, gathering examples on how leaders applied their learnings and resilience strategies impacting leader resilience practices. We will also assess participant attitudes to evaluate feasibility, acceptability, strengths, and areas for improvement of resilience training in leader contexts. A thematic analysis of participant experiences (Braun and Clarke, 2006) integrated into a framework for analyzing complex interventions, focusing on context, implementation, and mechanisms of impact (Moore et al., 2015) will be used to interpret this data, conceptualizing, and informing future resilience training initiatives. Together, these different process evaluation approaches aim to elucidate the *why* and *how* leader resilience training works, complementing the *what* from the statistical outcome evaluation.

### Data management and statistical analysis of results

2.7

*A priori* power calculations were conducted using G*Power 3.1 (Faul et al., 2007) to determine the required sample size for a repeated measure and ANOVA assessing the interaction between time (three waves) and group (intervention versus control). The analysis for repeated measures, within-between interaction, was based on the following parameters: a medium Cohen’s effect size (*f* = 0.25), a significance (Alpha) level of 0.05, desired power of 0.08, and correlation among repeated measures of 0.5 for two groups and three measurements. The power analysis indicated that a total sample size of 28 participants (14 per group) was deemed necessary to achieve 80% power to detect a group x time interaction in this multi-wave organizational trial. Potential attrition across waves is accounted for as indicated in the CONSORT 2010 Flow Diagram in Figure 3, illustrating sample size planning for 30% attrition, assuming attrition occurs evenly from recruitment and across the waves with a rate of approximately 10% throughout the study. However, the aim is to increase the final target sample size to approximately 100 participants to enhance the validity of the study, due to pressures from extreme times in the organizations.

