**Figure 3 fig3:**
[figure not shown]
CONSORT flow diagram for attrition.

Propensity scores, calculated via logistic regression, will ensure balanced covariate distribution between intervention and control groups, enhancing the validity and reliability of the randomized controlled study (Rosenbaum and Rubin, 1983). Participants will complete secure online questionnaires via Survey X-act, collecting sociodemographic data (age, gender, education) job-related factors (function, seniority, occupation, responsibility, functional area), and outcome data. Aggregated local baseline assessments (T0) will guide need analysis and curriculum adjustments, as recommended by reviewers of leadership training, to optimize learning and transfer (Lacerenza et al., 2017). Internal HR-trainers will be blinded to subsequent intervention data (T1, T2) to minimize training biases. Growth modeling procedures in leadership training have proven effective in evaluating leader changes during interventions (Day et al., 2021). SAS PROC MIXED (SAS Institute Inc, 2022) will be used to fit the Growth Model. An unconditional model will predict longitudinal data, followed by conditional linear growth models examining interaction effects (*p*-values) of person-level covariates on short-term (T0, T1) and long-term (T0, T2) trajectories for all primary outcome variables. Rasch analysis will calculate Cronbach’s Alpha (reliability), item fit, eigenvalues (dimensionality), and differential item function (DIF). Process evaluation data will be analyzed using the package “Markov chain” (Spedicato, 2017) for discrete time Markov chains, examining the progression of Kirkpatrick levels and relevant resilience factors implemented over time. Descriptive analysis will be performed using R (R Core Team, 2024) to show influencing factors on the leader resilience training and resilience processes. Participant data from Survey X-act will be managed by a designated research team member using unique participant codes and analyzed by an external statistician to reduce research biases. Data retention is set for 5 years post-study.

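### The arm effect is tested as change from T0 instead of being adjusted for T0, which at the plan's own correlation costs about a quarter of the precision of a single-wave comparison

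*Protocol article*

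**What the plan says.** All of this is in the protocol article, mainly section 2.7.

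- **Powered test.** The sample size is for a repeated-measures ANOVA "assessing the interaction between time (three waves) and group (intervention versus control". Its inputs are "a medium Cohen’s effect size (*f* = 0.25", "a significance (Alpha) level of 0.05" and "correlation among repeated measures of 0.5 for two groups and three measurements". The result is that "a total sample size of 28 participants (14 per group) was deemed necessary", and the article gives the purpose of that number as "to achieve 80% power to detect a group x time interaction in this multi-wave organizational trial". Section 2.3 defines the waves as T0 before, T1 during and T2 after the intervention, so the baseline is one of the three responses. The aim is then raised to about 100 leaders.
- **Planned outcome model.** The paragraph after Figure 3 describes linear growth models in PROC MIXED that test interactions of "person-level covariates on short-term (T0, T1) and long-term (T0, T2) trajectories for all primary outcome variables". T0 is again a response.
- **Use of T0 for adjustment.** Nowhere is a scale's T0 score named as a covariate, and nowhere are the arms given a common T0 mean. The one balancing device named is a propensity score, and its contents are not listed.
- **Allocation.** Section 2.5 specifies simple randomisation of individuals. Table 1 places the Allocation column before the Baseline (T0) column.

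**The concern.** When T0 is a response and the arm means are free at T0, the group-by-time term for two waves is the arm difference in mean change. Randomisation makes the true T0 means equal, and this contrast does not use that fact. It subtracts the whole T0 score. Adjustment subtracts only the part that predicts the follow-up score, which at a correlation of 0.5 and equal variances is half. The other half adds noise.

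The stake is efficiency in a small trial: 28 leaders are deemed necessary, about 100 are hoped for, and every primary scale is already measured at T0. Intervals come out wider and power lower than the same questionnaires would support.

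**Working it through.** **Inputs from section 2.7:** f = 0.25, alpha 0.05, correlation rho = 0.5, 2 groups, 3 measurements, N = 28, aim about 100. The target power is taken as 0.80. The parameter list prints 0.08, but the next sentence says 80%, and N = 28 fits only 0.80.

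**1. The plan's own figure.** For the within-between interaction, noncentrality = f² × N × m / (1 − rho), with 2 and 2(N − 2) degrees of freedom. At N = 28 this is 0.0625 × 28 × 3 / 0.5 = 10.5 on 2 and 52 df, giving power 0.812. At N = 26 power is 0.778. The smallest balanced N is therefore 28, as stated.

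**2. One follow-up wave (T0-T1 or T0-T2).** Variance per leader in SD² units, with equal variances and complete data:

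- change from T0: 2(1 − rho)
- adjusted for T0: 1 − rho²
- ratio: (1 + rho)/2

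| rho | change | adjusted | ratio |
|---|---|---|---|
| 0.3 | 1.40 | 0.91 | 0.65 |
| 0.5 | 1.00 | 0.75 | 0.75 |
| 0.7 | 0.60 | 0.51 | 0.85 |

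At rho = 0.5, the change contrast needs 1/0.75 = 1.33 times as many leaders for the same precision. A simulation of 20,000 trials with 50 per arm gave a ratio of 0.747. In one simulated data set, the two-wave mixed-model group-by-time coefficient and the arm difference in mean change were both 0.173.

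**3. Linear slope over three waves, rho = 0.5.** Code time as 0, 0.5, 1.

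- Free T0 means: variance factor (1 − rho) / Σ(t − mean t)² = 0.5/0.5 = 1.
- Common T0 mean: the inverse covariance is 2(I − 0.25J), where J is the matrix of ones. The information is 2(1.25 − 0.25 × 1.5²) = 1.375, so the factor is 1/1.375 = 0.727.

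The slope therefore loses slightly more than the single-wave contrast.

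**4. Omnibus 2-df test, rho = 0.5.** Noncentrality per unit of effect, for effects at (T1, T2):

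| Pattern | change | adjusted | ratio | loss |
|---|---|---|---|---|
| linear (0.5, 1) | 1.000 | 1.375 | 0.73 | 27% |
| step (1, 1) | 1.333 | 2.000 | 0.67 | 33% |
| T2 only (0, 1) | 1.333 | 1.500 | 0.89 | 11% |

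At N = 28 and the plan's f of 0.25, power would rise from 0.81 to about 0.92, 0.94 and 0.86 respectively.

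**5. Illustration at N = 100 (50 per arm), rho = 0.5.** SE for change = √(4 × 1.00/100) = 0.200 SD. SE adjusted = √(4 × 0.75/100) = 0.173 SD. The difference detectable with 80% power falls from (1.96 + 0.84) × 0.200 = 0.56 SD to 0.49 SD. For an assumed 0.5 SD difference at T2, the normal approximation gives Φ(2.50 − 1.96) = 70.5% and Φ(2.89 − 1.96) = 82.3%. The noncentral t gives 70% and 82%.

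**The case against.** **The model is not printed.** A three-wave model with a common T0 mean also has T0 as a response and also tests group by time, so it fits the quoted wording. The first quotation comes from the sample-size paragraph, and a full analysis plan may settle the matter. This stands in part. Free T0 means are the standard reading of a group-by-time ANOVA or growth model, and nothing in the article points the other way, but a reader should not take them as stated fact. Likewise, arm is only presumed to be among the person-level covariates whose interactions are tested.

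**The propensity score might already contain the T0 scores.** The article does not say what enters the score or how the score enters the outcome model. That use is neither confirmed nor excluded.

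**Stronger readings that a reader might infer, and why they fail.**

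- *The analysis is biased because an arm that starts worse by chance seems to improve more.* With a given imbalance this does happen. The chance T0 difference has an SD of √(2/14) = 0.38 SD with 14 per arm, and half of it passes into the change estimate at rho = 0.5. Over repeated randomisations, however, the estimate is unbiased. This shift is already part of the larger variance and is not a second defect.
- *The sample size is wrong.* It reproduces exactly for the test it powers.
- *Every version of the test loses a quarter.* That figure belongs to a single-wave contrast at rho = 0.5. The slope and the omnibus test lose different amounts (steps 3 and 4).

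**The remedy needs a clean T0.** Table 1 lists Allocation before Baseline, and leaders cannot be blind to weekly training. If they know their arm when they answer T0, randomisation no longer guarantees equal T0 means. This objection stands in full and becomes a condition of the fix.

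**Conclusion.** The point holds as a loss of efficiency. As described, the arm effect is a difference in change from T0, and adjusting for T0 would be more precise at almost no cost. At the plan's correlation of 0.5, the adjusted variance is 0.75 of the change-score variance for a single follow-up wave and 0.73 for a linear slope. The omnibus test loses about 11% to 33%. The single-wave saving shrinks as the correlation rises, from 35% at 0.3 to 15% at 0.7.

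These figures assume free arm means at T0, equal variances, the same correlation between all pairs of waves, complete data, and T0 answers unaffected by knowledge of the arm. The 0.5 SD effect behind the rise in power from 70% to 82% is an assumption made here for illustration.

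**What to change.** In section 2.7, state how T0 enters the outcome model. For each primary scale, either:

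- model T1 and T2 as responses in PROC MIXED, with that scale's T0 score (by wave) as covariate; or
- keep three waves as responses and give the arms a common T0 mean.

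Report the adjusted arm difference at each wave in scale points with a 95% confidence interval, not only an interaction p-value.

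State as well that T0 is completed before leaders are told their arm, since Table 1 leaves this open. If that cannot be ensured, do not impose the common T0 mean, and interpret T0-adjusted estimates with that caveat.

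The cost is a few lines of code and a sentence or two in section 2.7, with no extra questionnaires. The price in assumptions is reliance on T0 being unaffected by knowledge of allocation. N = 28 need not be recalculated on this account.

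### The sample size of 28 follows from its inputs, but the f = 0.25 called medium is a difference between arms of about 1.06 to 1.22 SD, and the desired power is misprinted as 0.08

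*Protocol article*

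**What the plan says.** Section 2.7 sizes the trial in one paragraph.

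- **Test.** It names G*Power 3.1 and a repeated-measures ANOVA of group by time: "The analysis for repeated measures, within-between interaction, was based on the following parameters".
- **Inputs.** The effect size is "a medium Cohen’s effect size (*f* = 0.25"). The other inputs are "a significance (Alpha) level of 0.05, desired power of 0.08, and correlation among repeated measures of 0.5", with two groups and three measurements.
- **Result.** The next sentence concludes that "a total sample size of 28 participants (14 per group) was deemed necessary to achieve 80% power to detect a group x time interaction".
- **Attrition and target.** The paragraph then refers to planning for 30% attrition, shown in a flow diagram that is not reproduced in the text at hand. It adds that "the aim is to increase the final target sample size to approximately 100 participants", which it justifies by the validity of the study and not by any power figure.

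Nowhere does the article translate f into a difference between arms, either in SD units or in points on any of the five primary scales.

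**The concern.** In a plain comparison of two groups, f = 0.25 equals a standardised difference of 0.5, and that is what most readers understand by a medium effect. A total of 28 for 80% power is far too small for such a difference in a parallel-group trial, even with repeated measures. Either the calculation is wrong, or f stands for something larger here than the label suggests. The two power figures in adjacent sentences, 0.08 and 80%, add to the doubt.

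At stake is how the results will be read. A reader who accepts that 28 is enough for a medium effect could take a null result as evidence against a moderate benefit. The larger target of about 100 gives that reader no help, because no detectable difference is attached to it.

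**Working it through.** **Inputs from section 2.7.** f = 0.25; alpha = 0.05; correlation rho = 0.5; k = 2 groups; m = 3 waves; N = 28, 14 per group; attrition 30%; target about 100.

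**Step 1: reproduce 28.** For a within-between interaction under the convention that puts the repeated-measures gain into the noncentrality, with sphericity:

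- lambda = f² × N × m / (1 − rho) = 0.0625 × 28 × 3 / 0.5 = 10.5
- df1 = (k − 1)(m − 1) = 2; df2 = (N − k)(m − 1) = 26 × 2 = 52
- power from the noncentral F = 81.2%; N = 26 gives 77.8%

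So 28 is the smallest even total that reaches 80%. A target power of 0.08 would already be met at a total of 4, so 0.80 was the value used.

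**Step 2: what f = 0.25 means as a difference between arms.** Here f is the SD of the interaction cell effects divided by the within-group SD. Let d_t be the difference between arms at wave t in SD units, with d = 0 at T0 because of randomisation. Then f² is the mean over the three waves of ((d_t − mean d)/2)².

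- *Linear divergence, (0, d/2, d).* The mean is d/2 and the halved deviations are −d/4, 0, d/4. So f² = (d²/16 + 0 + d²/16)/3 = d²/24, and d = 0.25 × √24 = 1.22 SD.
- *Step, (0, d, d).* The mean is 2d/3 and the halved deviations are −d/3, d/6, d/6. So f² = (d²/9 + d²/36 + d²/36)/3 = d²/18, and d = 0.25 × √18 = 1.06 SD. A late effect, (0, 0, d), gives the same value.

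Simulation with 14 per arm, equal correlations of 0.5 and 20,000 trials gives 80.8% power at 1.22 SD (linear) and 81.1% at 1.06 SD (step), which confirms the conversion.

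**Step 3: power if medium is taken as 0.5 SD (assumption).** f = 0.5/√24 = 0.102 (linear) or 0.5/√18 = 0.118 (step or late). The test is the same as in step 1.

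| Analysed | Linear | Step or late |
|---|---|---|
| 28 | 19.3% | 24.5% |
| 70 (100 × 0.7) | 44.1% | 56.1% |
| 100 | 59.6% | 72.9% |

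Simulation at 28 gives 19.0% and 24.0%. By this test, 80% power for 0.5 SD needs 156 (linear) or 118 (step or late) completers.

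**Step 4: detectable difference in the T0–T2 contrast at 80% power.** The variance of the change score is 2(1 − rho) = 1 in SD² units, so SE = √(2/n) with n per arm. With baseline adjustment the residual variance is 1 − rho² = 0.75, so SE = √(0.75 × 2/n). Two-sided t test, alpha 0.05:

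| Analysed (per arm) | Change score | Baseline-adjusted |
|---|---|---|
| 28 (14) | 1.10 SD | 0.95 SD |
| 70 (35) | 0.68 SD | 0.59 SD |
| 100 (50) | 0.57 SD | 0.49 SD |

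For a 0.5 SD difference at 28, the change-score contrast has about 25% power.

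**The case against.** The strongest reply is that nothing stated is false on its own scale. The paragraph names the program, the option and every input; 28 follows from them; and 0.25 is the conventional medium value of f. The article never mentions 0.5 SD or any difference between arms, so the low power figures rest on a benchmark brought in from outside. All of that stands, and it rules out the reading that 28 is miscalculated. It does not rescue the label. The convention that gives 28 already has m/(1 − rho) in the noncentrality, and with it f = 0.25 requires more than 1 SD between arms. If f = 0.25 is entered under the program's other convention, lambda = f² × N, power at 28 is 19.3% and about 158 are needed. The figure of 28 therefore depends on pairing the conventional label with a convention under which it no longer means what readers expect.

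Three further replies also have force.

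- **The target is about 100, not 28.** A reader might infer from the 19–25% figure that the trial as planned has only about a one-in-five chance of detecting a moderate effect. The document does not support that. With 100 analysed and baseline adjustment, the detectable difference is 0.49 SD. But the article does not say whether 100 are recruited or completing, and 28 remains the number called necessary.
- **0.08 is a slip.** A reader might infer that the design power is in doubt. It is not, since the next sentence says 80% and only 0.80 gives 28.
- **The planned contrasts.** The analysis looks at T0–T1 and T0–T2 trajectories, while the calculation powers a 2-df interaction. A reader might treat this as a separate flaw. It changes little: 25% against 19–25% at 28 for 0.5 SD.

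**Conclusion.** The concern holds as one about how the effect size is described, not as an arithmetic error. The total of 28 gives 80% power only for a difference between arms of about 1.1 to 1.2 SD at T2, more than twice the 0.5 SD that medium suggests for two groups. The target of about 100 has no detectable difference stated; in the T0–T2 contrast it is about 0.57 SD if 100 are analysed and 0.68 SD if 70 are. The 0.08 is an editorial slip with no effect on the sample size.

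The conversion assumes equal arms at T0 and a difference that does not reverse sign between T1 and T2; only a reversal would bring f = 0.25 below 1.06 SD, and that does not fit the hypothesis of sustained or improved outcomes. The figures also take rho = 0.5 from the plan, equal correlations across waves, alpha 0.05 and no clustering. The 0.5 SD benchmark is an assumption, as is the case of 70 analysed, which reads the 30% attrition as applying to 100 recruited. Severity is moderate: design, enrolment and analysis all stand, but a figure that readers will rely on is misdescribed.

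**What to change.** Reword the sample-size paragraph of section 2.7:

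1. Correct the desired power from 0.08 to 0.80.
2. Keep f = 0.25, name the effect-size convention used, and qualify or drop the word medium. State that 28 gives 80% power only for a difference between arms of about 1.1 to 1.2 SD at T2.
3. Say whether the target of about 100 means recruited or completing.
4. State the difference detectable with 80% power in the T0–T2 contrast at that target: about 0.57 SD if 100 are analysed or 0.68 SD if 70 are analysed; about 0.49 and 0.59 SD if the analysis adjusts for baseline.

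The cost is one paragraph. No extra enrolment is needed. The drawback for the sponsor is that the stated figure becomes less favourable.
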